### Statistics

#### Statistical considerations and sample size calculation

A worldwide accepted practice after open or minimally invasive oesophagectomy is to place apical and basal chest drains for complete drainage of the pleural cavity. The sample size calculation is based on a comparison of double versus single chest drain applications after pulmonary lobectomies. In a prospective randomized trial, the mean values of postoperative pain according to the visual analogue scale (VAS) on the second postoperative day were 4.28 in the single-drain group *versus* 5.10 in the double-drain group (*p* = 0.001). Furthermore, the authors described a significant reduction in the amount of drainage fluid (600 ml vs. 896 ml). The authors concluded that the insertion of two chest tubes is not more effective than a single chest tube after lobectomy. In addition, the absence of chest tubes causes significantly less postoperative pain [21, 22]. These results are supported by the results of another study group that found a significant difference in the maximum postoperative pain score when comparing one with two postoperative chest drains [21, 22]. The sample size estimation for the present trial was therefore based on a reduction of pain scale measured by NRS from five points in the group with drains to four points in the intervention group on POD 2 and assuming an equal standard deviation of 1.4 for both groups. To achieve 80% power with a two-sided *t*-test for two independent groups and a significance level of 5%, a group size of 32 patients is necessary. With an estimated dropout rate of 10%, the total sample size was calculated with 72 patients with 36 in each of the two groups. Sample size calculation was performed using the SAS 9.4 software (Cary, NC 27,513–2424, USA). Confirmatory analysis of the primary endpoint will be carried out by a two-sided *t*-test for independent groups on a modified intention-to-treat population, which comprises all patients randomized with successful RAMIE. Statistical significance will be set at 0.05. Secondary endpoints will be analysed by Fisher’s exact test, Student’s *t*-test, Mann–Whitney *U* test, mixed models, and Kaplan‒Meier method, as appropriate. Sensitivity analyses will be conducted on the per-protocol set. Statistical analyses will be performed using the R statistics software package (version 3.1.3 “or higher”, the R Foundation for Statistical Computing). No interim analysis of primary or secondary endpoints of efficacy is planned.

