### Trial design, study registration, and ethics

The title of this clinical trial is “Drainless Robot-assisted Minimally Invasive Oesophagectomy” (RESPECT Trial). The study is designed as a randomized controlled multicentric, two-arm parallel-group superiority surgical trial with an interventional group (A: robot-assisted minimally invasive oesophagectomy with early removal of the chest drain) and a control group (B: robot-assisted minimally invasive oesophagectomy with chest drains). The study is coordinated by the leading Study Center of the Department of Visceral, Thoracic and Vascular Surgery, Universitätsklinikum Carl Gustav Carus, Technische Universität Dresden, Germany.

Participating centres at the trial commencement are the two certified university centres: the Department of Visceral, Thoracic and Vascular Surgery, Universitätsklinikum Carl Gustav Carus, Technische Universität Dresden, Germany, and the Department of General, Visceral and Transplantation Surgery, University Hospital Heidelberg, Heidelberg, Germany. Additional centres can be evaluated for participation if equivalent standards for the operation (RAMIE procedure with equal technique) and trial management can be guaranteed at these sites. The trial was registered in advance at ClinicalTrials.gov (https://clinicaltrials.gov/ct2/show/NCT05553795). The study protocol was approved by the Ethical Committee at the Technische Universität Dresden (BO-EK-77022021). Any modifications to the protocol will require a formal amendment of the protocol. Amendments will be re-evaluated and approved by the responsible independent ethics committees. The principal investigator will notify the participating centres and send a copy of the revised protocol to the responsible investigator to add to the Investigator Site File. Furthermore, an update of the trial register will be initiated.

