### Assignment and randomization

All patients will be screened for eligibility considering the inclusion criteria on the day of admission (standard: the day before the surgery). Screened and eligible patients will be included in the trial after obtaining written informed consent. After obtaining written informed consent, randomization will be performed intraoperatively after completion of the oesophagogastrostomy and verification of the exclusion criteria. To achieve comparable intervention groups for known and unknown risk factors, randomization will be performed using block randomization with variable block length. Randomization lists are stratified by trial sites and will be centrally generated by nQuery by the Coordination Centre for Clinical Trials. A patient will be randomized by authorized trial personnel using the electronic REDCaP® system.

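### The confirmatory t-test ignores site, although randomisation is blocked within site; if sites differ in POD 2 pain, the test is conservative and some power is forgone

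*Protocol article*

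**What the plan says.** In the protocol article, Assignment and randomization states that "randomization will be performed using block randomization with variable block length" and that "Randomization lists are stratified by trial sites and will be centrally generated by nQuery". Under Trial design, study registration, and ethics, "Participating centres at the trial commencement are the two certified university centres", and further centres may be added.

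Statistical considerations and sample size calculation then fixes the primary analysis: "Confirmatory analysis of the primary endpoint will be carried out by a two-sided *t*-test for independent groups", in the modified intention-to-treat population. No site term or stratified test is named for the primary endpoint. Mixed models appear only in the list of methods for secondary endpoints, and the only sensitivity analysis named is on the per-protocol set. The sample size rests on the same unadjusted t-test.

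The confirmatory method is thus stated outright. It is not a detail left open for a separate analysis plan.

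**The concern.** Blocking within site keeps the arms nearly balanced on site. A difference in pain level between sites then affects both arm means alike and largely cancels from their difference. The two-sample t-test does not know this. It treats the arm means as independent and leaves the between-site variance in its pooled SD.

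If sites differ, three things follow: the confidence interval is wider than it need be, the true type I error is below the nominal 5%, and a real effect is somewhat less likely to be detected than under an analysis that respects the design. Planned power is only just above 80%, so there is little reserve.

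Site differences are possible on the article's own account. Surgical technique allows some variation between centres, and Perioperative pain management has a pain service adjust the epidural to each patient.

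**Working it through.** **Inputs from the article** (Statistical considerations and sample size calculation): means going "from five points in the group with drains to four points in the intervention group on POD 2", so a difference of 1.0; "assuming an equal standard deviation of 1.4 for both groups"; two-sided 5% level; 80% power; 32 evaluable per group. "With an estimated dropout rate of 10%, the total sample size was calculated with 72 patients with 36 in each of the two groups".

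**Assumptions, because the article gives no figure:** the share r of outcome variance that lies between sites (0 to 20%), two sites of equal size, and exact balance of arms within site.

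**1. The plan's own figure.** The t-test's standard error is 1.4 × √(2/32) = 0.35, so the noncentrality is 1.0/0.35 = 2.86 on 62 degrees of freedom. Power from the noncentral t-distribution is 0.790 at 31 per group and 0.803 at 32, so 32 is right. With 10% dropout, 32/0.9 = 35.6, rounded up to 36 per group and 72 in total. The stated figures reproduce.

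**2. The mechanism, with 1.4 as the total SD.** The t-test's standard error stays at about 0.35 whatever r is. With balance within site, the true standard error is 0.35 × √(1 − r):
- r = 5%: 0.341 (simulated 0.342)
- r = 10%: 0.332 (simulated 0.334)
- r = 20%: 0.313 (simulated 0.312)

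The gap between two equal sites that corresponds to r is 2 × 1.4 × √r. For example, 2 × 1.4 × √0.10 = 0.89 NRS points.

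**3. Consequences, 1.4 as total SD.** Simulation of 40,000 trials per setting, t-test versus a linear model with arm and site:

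| Site share r | Site gap (NRS) | Type I error, t-test | Type I error, adjusted | Power, t-test | Power, adjusted |
|---|---|---|---|---|---|
| 0% | 0 | 4.8% | 4.8% | 80.4% | 80.4% |
| 1% | 0.28 | 4.9% | 5.0% | 80.1% | 80.4% |
| 2% | 0.40 | 4.6% | 4.8% | 80.4% | 81.0% |
| 5% | 0.63 | 4.5% | 5.1% | 80.7% | 82.1% |
| 10% | 0.89 | 3.8% | 4.8% | 81.4% | 84.2% |
| 20% | 1.25 | 2.8% | 4.9% | 82.9% | 88.4% |

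The simulation standard error is about √(0.8 × 0.2/40,000) = 0.2 percentage points for power and √(0.05 × 0.95/40,000) = 0.1 points for type I error. A separate run of 100,000 trials per setting at 10% and 20% agreed: power 81.6% vs 84.4% and 82.8% vs 88.2%, t-test type I error 3.8% and 2.8%.

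**4. Consequences, 1.4 as within-site SD.** The article does not say which SD is meant. On this reading the total variance is 1.4²/(1 − r), and the t-test's standard error grows with it, to 0.391 at r = 20% against a true value of 0.35.

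| Site share r | Site gap (NRS) | Power, t-test | Power, adjusted |
|---|---|---|---|
| 5% | 0.64 | 78.8% | 80.2% |
| 10% | 0.93 | 76.9% | 80.1% |
| 20% | 1.40 | 73.1% | 80.4% |

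**The case against.** The case against giving this much weight is fair on several counts.

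- **The loss is conditional.** It arises only if mean POD 2 pain differs between sites, and the article gives no site means, site variance or intraclass correlation. At a 1 to 2% share the loss is 0.3 to 0.6 points of power, which is negligible. This stands.
- **The protocol works against large site effects.** It sets common surgical guidelines and a minimum surgeon experience, describes one epidural and analgesic regimen, admits further centres only on equivalent operative standards, and uses trained assessors from outside the surgical and ward teams. A 20% share implies a gap of 1.25 points, more than the treatment effect itself, and is best read as an upper scenario. This stands too, although none of these measures rules out a difference between sites.
- **Equal sites are the least favourable split for the t-test.** For a 0.89-point gap, an assumed 75:25 split gives a between-site variance of 0.75 × 0.25 × 0.89² ≈ 0.15, or about 7.5% of 1.4² = 1.96, against 10% with equal sites.

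A reader might go further and infer that the test is invalid, that type I error is inflated, or that the sample size is wrong. The article supports none of these. The error runs in the conservative direction, so a significant t-test result can be trusted. The sample size was computed for this same test and reproduces. With 1.4 as the total SD, the planned test meets its 80% target across the whole range examined, so only part of the benefit of stratification is forgone. A shortfall below 80% needs both a site difference and the within-site reading of the SD.

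**Conclusion.** The mismatch between design and analysis is real: site is used to randomise and then dropped from the confirmatory test. It is a modest matter of efficiency and calibration, with no bias.

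On the total-SD reading, the power forgone is nil with no site effect, about 1.4 points at a 5% share, 2.8 at 10% and 5.5 at 20%, while the true type I error drifts from 5% to about 4.5%, 3.8% and 2.8%. On the within-site reading, the forgone power is about 1.4, 3.2 and 7.3 points at those shares, and the t-test misses its 80% target.

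These sizes rest on assumed site shares, two equal sites and balance within site. The direction of the effect does not depend on the particular share assumed. The change is worth making because it costs almost nothing and showed no measurable loss of power when sites did not differ.

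**What to change.** Replace the t-test as confirmatory analysis by a linear model of POD 2 NRS on arm and site. Report the adjusted mean difference with its 95% confidence interval as the primary result, and keep the unadjusted t-test as a sensitivity analysis.

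If further centres join, state before the analysts are unblinded the minimum number of patients for a site to have its own term and the rule for pooling smaller sites. Without a fixed threshold and rule, pooling would bring analyst discretion into the confirmatory model.

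The cost is a short amendment to the statistics section, one degree of freedom with two sites and one more for each site added. The sample size stays as it is, and no further patients or data are needed, since site is already recorded for randomisation.

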
### Blinding

Blinding of participants, research assistants, operating surgeons, data collectors, and outcome assessors to the treatment allocation is not feasible. Postoperative blinding of patients and outcome assessors is not possible since unblinding would occur when vacuum suction was removed before the assessment of the primary endpoint. Outcome assessment will be carried out by trained study personnel who are not part of the surgical or ward team to guarantee objectivity. Data analysts will be blinded to the intervention.

### Data processing

#### Patient education and written informed consent

All consecutive patients were screened for potential inclusion by the investigator at the respective participating centres. Eligible patients are asked for informed consent. Before randomization, each patient will be informed by authorized investigators about the nature, objectives, expected benefits, and potential risks of the trial. Each patient must declare his or her willingness to participate in the study verbally and in writing after being informed in a manner that he or she can understand. Each patient must be informed that he or she is allowed to withdraw their informed consent verbally or in written form at any time without receiving any reprisals or disadvantages. In the event of revocation of the declaration of consent, the data stored up to this point in time will continue to be used without naming a name if this is necessary to evaluate the effects of the investigational product and to ensure that the interests of the person concerned worthy of protection are not impaired.

### Data collection

After the patient gave his or her informed consent, the demographic and basic data (sex, age, weight, height, medical history, current medication, comorbidities, ASA classification, ECOG status), and primary tumour characteristics (UICC classification, date of diagnosis, location, previous treatments including chemotherapy, target therapy, radiotherapy, and surgery) are evaluated and documented by the investigator. Intraoperative parameters such as length of operating time, blood loss, blood transfusion requirement, and conversion to open surgery are recorded.

During each study visit and on the day of discharge, primary and secondary endpoints and SAEs are evaluated and documented according to the eCRF. During the postoperative visits, routine blood tests (including haemoglobin concentration, leucocyte count, and serum C-reactive protein) will be performed. Furthermore, data that will be collected within these study visits include at least the following: postoperative assessment, ICU length of stay, grading of complications according to Clavien‒Dindo Classification, morbidity and mortality within the hospital stay, length of hospital stay, drain secretion volumes, postoperative examinations (e.g. chest X-rays, CT scans), and physical activity of the patient. The physical activity of the patients is collected using a CE-certified fitness tracker device, which measures the number of steps, distance, and activity minutes during the hospital stay. The transmission of these data works automatically via synchronization with a tablet or is carried out by the investigators before discharge.

### Documentation

It is the responsibility of the investigator to ensure that the study is conducted in accordance with the professional code for physicians, the Declaration of Helsinki in its current version, and the study protocol and that the data are properly documented. All data collected in this study must be entered into the eCRF by appropriately authorized persons. This also applies to data from persons who have been excluded from the study. The study site records participation on a patient identification list. This list is used for the identification of the participating persons and contains the patient number, full name, date of birth, and date of admission to the RESPECT trial. The patient identification list remains at the trial centre after the study is completed.

Using the audit trail in the REDCaP® online database, all data and corrections are automatically logged with the date, time, and the person making the entry so that former entries can be retrieved at any time.

Records and documents related to the RESPECT trial (e.g. documentation of informed consent, worksheets, and other relevant documents) must be retained by the investigator for 10 years in accordance with Good Clinical Practice.

### Data management and quality assurance

Day-to-day support for the trial is provided by the principal investigator who will take supervision of the trial and the medical responsibility. All data management will be performed in the REDCaP® online database. The entered data are managed and processed by the study centre of the Department of Visceral, Thoracic, and Vascular Surgery, University Hospital Carl Gustav Carus, TU Dresden, the Department of General, Visceral, and Transplantation Surgery, Heidelberg University Hospital and further participating centres in accordance with data protection regulations.

The data are checked by range, validity, and consistency checks. The site staff is responsible for data correction. A statement must be provided for any missing data.

The data manager will supervise and support the solution of data discrepancies and will close all correctly resolved discrepancies. If an outstanding entry cannot be solved, the data manager may close the entry. At the end of the study, the database will be closed after all relevant data according to the study protocol have been entered. Thereafter, any changes to the database are possible only by a joint written agreement between the coordinating investigators and the data manager.

#### Data Monitoring Board (DMB)

In case of any irregularities, for example, concerning the prevalence or type of adverse events or serious adverse events reported to the principal investigator, the members of the independent DMB will be informed without any delay. The independent DMB will receive regular reports about major complications after 20 and 40 patients have been randomized. The results of the risk and safety analysis will be reported to the principal investigator, including recommendations concerning the continuation or termination of the trial.

Monitoring will be conducted according to approved standard operating procedures, which include personal site visits with verification of source data. Clinical monitoring in the RESPECT study will be performed according to the International Conference of Harmonization (ICH) Good Clinical Practice (GCP) guidelines by the Study Center of the Department of Visceral, Thoracic, and Vascular Surgery of the University Hospital and Medical Faculty Carl Gustav Carus, Dresden. The monitoring procedures are predefined in a study-specific monitoring manual and adapted to the study-specific risks for the patients. Regular on-site monitoring visits are planned at all sites depending on the recruitment rate and quality of the data (approximately one visit per site and year). The investigator must allow the monitor to look at all essential documents and must always provide support to the monitor. Study progress, recruitment, and data capture will also be reviewed at the leading centre by the principal investigator and study coordinators.

The role of the Steering Committee is to provide overall oversight of the trial and ensure that it is conducted according to the rigorous standards as outlined in the Guidelines for Good Clinical Practice.

### Ethical considerations

According to the Medical Association’s Professional Code of Conduct “Ärztliche Berufsordnung” of each participating German state, an independent Ethics Committee (IEC) must be consulted before the start of the clinical study concerning questions relating to professional ethics and legal issues, which are associated with the study. For this purpose, the study protocol, patient information sheet, and informed consent must be submitted to the responsible Ethics Committee.

The trial will be conducted in line with the Declaration of Helsinki in its current version and with the laws and declaration of the concerned country. This protocol is designed to ensure that the study is carried out and analysed according to ICH-GCP. The trial is in line with the Consort Guidelines [23].

## Discussion

In the past, the removal of chest drains after oesophageal resections were often determined by the daily amount of secretion. For many surgeons, a daily secretion of less than 200 ml in 24 h represented a cut-off value from which drainage could be safely removed. However, these values were based on prevailing doctrine and the concern of having to reinsert a chest drain rather than on a well-founded scientific data [14].

Enhanced recovery after surgery (ERAS) protocols after oesophagectomy can additionally lower morbidity but still include thoracic chest drains for a minimum of a week after the operation. Reduction in the number and early removal of chest drains has already been advocated after pulmonary resections.

The current data show that more aggressive chest drain removal strategies under ERAS programmes are safe and feasible. For example, a threshold of 500 ml per 24 h led to recurrent pleural effusion after video-assisted thoracic surgery in only 2.8% of patients [24]. However, at a daily secretion of 450 ml, removal of the chest drain was no longer associated with recurrent pleural effusion [25]. Therefore, the authors concluded that removal of the drain seems to be possible if there is no evidence of air leakage, pneumothorax, chyle leak, purulent secretion, or active bleeding.

Regarding the number of chest drains, several studies have shown that the insertion of two chest tubes is not superior to the insertion of a single chest tube after pulmonary lobectomy. The use of one chest tube is more effective than the use of two tubes because it causes less postoperative pain, less pleural effusion, and reduced chest tube duration without affecting postoperative morbidity [22, 24, 26]. Referring exclusively to postoperative pain, the data show a significant reduction between two and one chest drain on the second day after surgery [21, 22, 26]. In addition, one study revealed a significant decrease in the course of the second postoperative week [22].

There are no reports of randomized controlled trials investigating the potential advantages of modern RAMIE for oesophageal cancer without postoperative abdominal and chest drains compared to the postoperative use of chest drains, which is considered standard practice worldwide. This randomized controlled multicentric trial was therefore initiated to assess whether avoidance of chest drains during the postoperative course after RAMIE can significantly reduce postoperative pain, improve functional recovery, and shorten hospital stay compared to the use of chest drains. Avoidance of chest drains during the postoperative course is achieved by the removal of a chest drain 3 h after the end of the surgical procedure. The current standard in consensus fast-track protocols after oesophagectomy is the removal of chest tubes on POD 6 [13, 21]. The 3-h period is necessary and sufficient to enable complete expansion of the right lung and to exclude a persistent air leak. This concept has been successfully applied in daily practice after RAMIE in selected cases at the authors’ institution. Its implementation in everyday use would first and foremost be a step forwards for our patients. The healthcare system would benefit from shorter hospital stays and associated cost savings. Finally, it would be a step forwards for surgical science because the reduction of postoperative morbidity is both a key aim and a major driver of surgical innovation.

This study aims to compare two different chest drain management strategies in patients undergoing RAMIE for oesophageal cancer with regard to perioperative complications until discharge. The study’s primary objective is to investigate whether the intensity of postoperative pain can be significantly reduced by avoiding thoracic drains after RAMIE. We assume that this will influence secondary endpoints such as early recovery and length of hospital stay.

